#### Use of harm reduction strategies

Use of 6 harm reduction strategies to decrease the occurrence and impact of reproductive and sexual coercion and unsafe relationships was assessed at both follow-up visits. Participants are asked to endorse whether they had used these strategies (e.g., “have you hidden your birth control from your partner because you were afraid he would get upset with you for using it” and “have you tried to protect yourself from your partner by asking family or friends to call or text you when you were with that partner”) in the past 3 months (Cronbach alpha = 0.39). The outcome is modeled as a summary score with a maximum value of 6 (one point per each strategy endorsed). To prevent measurement bias, this construct is assessed at follow-up visits only (T2 and T3).

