#### Self-efficacy to implement harm reduction strategies

Participants are presented with four statements that are designed to assess level of confidence in implementing behaviors to reduce the impact of reproductive and sexual coercion (e.g., “If my sexual partner is keeping me from using birth control, I am confident I could ask a healthcare provider about other kinds of birth control that my partner can’t mess with.”). Responses are rated on a 5-point Likert scale from “strongly agree” to “strongly disagree” with the outcome modeled as a mean response to the 4 items (Cronbach alpha = 0.72). To reduce measurement effect (i.e., the survey items themselves increasing women’s knowledge of harm reduction strategies), this construct is assessed at follow-up visits only (T2 and T3).

We also collected a general self-efficacy measurement at baseline, using The New General Self-Efficacy scale (NGES) developed by Chen, Gully, and Eden [89] to acquire the statistical power-enhancing advantages of a baseline covariate that is correlated with the above self-efficacy outcome, but whose assessment would not lead to a “measurement effect.” The NGES consists of 8 items (e.g., “Even when things are tough, I can perform quite well.”) with response options on a 5 point Likert scale (“strongly agree” to “strongly disagree”) (Cronbach alpha = 0.89). General self-efficacy is modeled as the mean response to these items and the baseline value is included as a covariate in the models assessing self-efficacy to implement harm reduction strategies.

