#### Knowledge of IPV-related resources and services

To assess knowledge of IPV-related resources and services, participants are presented a list of resources and asked to endorse each one for which they “had received information on in the past 3 months” (Cronbach alpha = 0.80). Listed resources included Domestic Violence Advocacy Services, Rape Crisis Center, National Domestic Violence Hotline, Teen Dating Abuse Helpline, and Loveisrespect.org. A summary score is calculated with one point per resource selected for a maximum score of 5. To reduce the possibility of participants endorsing items because they had seen the resources identified in earlier surveys, this measure was not included in the baseline survey.

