#### Use of IPV-related resources and services

Participants are asked to endorse all IPV-related resources that they used in the past 3 months from the same list presented in the measure of knowledge of IPV-related resources and services (above) (Cronbach alpha = 0.55). As with the knowledge measure, this question is presented at follow-up visits only (T2 and T3). The outcome is modeled as a summary score, tallying number of endorsed items.

*Disclosure to a health care provider* was assessed at T3 only with two questions: whether in the past 12 months the client told a health care provider about ever being in an unhealthy or unsafe relationship or about a partner trying to get her pregnant when she didn’t want to be, messing with birth control, or controlling a pregnancy.

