At the conclusion of T3 data collection, available FP medical records are reviewed for participants who had signed authorizations allowing the study team to do so (98 % of participants). RAs review visits spanning 12 months pre-baseline to 18 months post-baseline to record number and types of clinic visits, reasons for visits, pregnancy and STI testing and diagnoses, documentation of assessment for IPV and RC, and documentation of any disclosures of IPV or RC.

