### Power calculations and sample size

The planned recruitment of 3600 subjects from 25 clinics in 17 clusters was designed to achieve 80 % power to detect clinically significant effects of the intervention (under two-sided testing at alpha = 0.05) for each of the specific hypotheses, after making appropriately cautious adjustments for loss to follow-up, variance inflation arising from cluster randomization, repeated follow-up measurements (of most outcomes), the small number of denominator degrees of freedom available when 17 clusters are used to assess the effect of the intervention, and for the restriction of the Aim 2 analyses to subjects who reported recent IPV or RC victimization at baseline. Reduction of RC and IPV by 50 % (*OR* = 0.50) in both the full sample and subset experiencing IPV/RC at baseline were specified as clinically significant effects. We also specified that reduction in recent unintended pregnancy at the 12-month follow-up by 43 % (*OR* = 0.57) in the full sample would represent a meaningful clinical effect. Clinically significant effects were also specified for other primary and secondary outcomes, corresponding to intervention effect sizes of 0.20 standard deviations and 0.35 standard deviations for Aim 1 and Aim 2 analyses, respectively.

Calculations were guided by results from our pilot study, [26] allowing us to anticipate that the prevalence of recent reproductive coercion in the control group would be 10 % in the Aim 1 sample and 26 % in the Aim 2 sample and we powered the study to detect reduced prevalence of this outcome in the intervention arm of 5.3 % and 14.9 % in the Aim 1 and Aim 2 analyses, respectively. Similarly, assuming the prevalence of recent unintended pregnancy is 20 % in the control arm at the 12-month follow-up (from pilot data), our study was powered to detect a prevalence reduced to 12.5 % in the intervention arm in the Aim 1 analysis.

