Based on results from the pilot study, we anticipated retaining at least 80 % of baseline subjects for the first follow-up assessment. We further assumed that at least 75 % of the subjects from the first follow up would also complete the second follow-up assessment, that approximately 17 % of subjects would report recent IPV victimization at baseline. To account for cluster randomization design effects, we assumed that in our planned regression analysis the residual within-person and within-clinic correlations would be no higher than 25 % and 1 % respectively for key outcomes. The above conditions indicate that our planned sample size of 3600 patients and repeated measurements for most outcomes would result in analyses that would provide an effective sample size for Aim 1 analyses of at least 798 for assessing the unintended pregnancy outcome (at the 12-month follow-up) and at least 1000 for the other Aim 1 outcomes (where observations at both follow-up occasions would be analyzed jointly – i.e., pooled T2 and T3 data). For the Aim 2, we anticipated an effective sample size of at least 424 observations for the other key outcomes in Aim 2 (where assessments from both follow-up occasions would be analyzed jointly). If attained, these effective sample sizes, based on prudently cautious assumptions, ensure at least 80 % power to detect clinically significant effects for the main outcomes in the analyses for Aims 1 and 2.

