#### Outcome analyses

We will use generalized linear mixed effects models for evaluating the effect of the intervention on follow-up outcomes. Separate models will be created for each outcome, and predictors will include a parsimonious set of important covariates, including potential confounders identified in preliminary analyses, the baseline measure of the outcome (when available), and a clinic-level binary indicator for whether the patient was in a treatment (vs. control) clinic. Random effects will be specified to account for the nesting of patients within clinic and, where appropriate, for repeated follow-up measurements. Recognition of sexual coercion, reproductive coercion, and physical and sexual partner violence baseline measures will be available for all time points and thus baseline measures will be included as covariates in the respective models to improve the precision of our estimated intervention effects. Within-clinic and within-patient cluster effects will be specified as random effects in the models.

For Aim 2 hypotheses, the analysis will be restricted to the patients who report at baseline having recently experienced physical or sexual partner violence or reproductive coercion.

Following the definitive assessments of key study hypotheses, a series of exploratory analyses will be conducted. In particular, the potential for differential impact of the intervention based on patient characteristics will be evaluated, with a view toward identifying factors (e.g., race/ethnicity, age, immigrant status, involvement in commercial sex) that may facilitate or impede the efficacy of the intervention, and to identify patient subgroups most receptive to the intervention or that may require further assistance.

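### Four follow-up-only outcomes have no named baseline proxy: the T1 reproductive coercion and partner violence scores are not prespecified for them and would enter only through a p < .20 imbalance screen

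*Protocol article*

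**What the plan says.** Four secondary outcomes have no T1 value in the protocol article.

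- Use of harm reduction strategies: "To prevent measurement bias, this construct is assessed at follow-up visits only (T2 and T3".
- Knowledge of IPV-related resources: "this measure was not included in the baseline survey".
- Use of IPV-related resources: "this question is presented at follow-up visits only (T2 and T3".
- Disclosure to a provider: asked at T3 only.

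A fifth outcome, self-efficacy to implement harm reduction, is also measured only at follow-up. There the plan collects a general self-efficacy scale at T1 "to acquire the statistical power-enhancing advantages of a baseline covariate that is correlated with the above self-efficacy outcome" and fixes it as a covariate.

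Under Outcome analyses, each model takes the outcome's own baseline value where one exists, plus confounders found in preliminary analyses. For recognition of coercion, RC and IPV, "baseline measures will be included as covariates in the respective models to improve the precision of our estimated intervention effects". The Overview of the Planned analytic approach adds that arms are compared on key baseline measures and that any variable differing at p < .20 joins the adjusted models. It gives both imbalance and precision as reasons for covariates.

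**The concern.** The plan recognises that a follow-up-only outcome loses the precision of a baseline covariate, and it repairs this for one such outcome out of five. For the other four the own-baseline clause is empty and no substitute is named, although an obvious candidate is already collected. The example items for harm reduction use (hiding contraception from a feared partner, arranging for friends to call while with him) presuppose a coercive or unsafe partner, so T1 RC and IPV should predict the answer.

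As the rules stand, the T1 scores reach these models through a test of between-arm difference. Such a test does not ask whether the covariate predicts the outcome. Under randomisation a valid test at p < .20 leaves a given covariate out about 80% of the time, however prognostic it is. At stake is a small loss of precision, a small residual imbalance in the Aim 1 contrasts, and a covariate set that is settled only after the arms have been compared.

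**Working it through.** **1. The plan's own power figure.** Inputs from Power calculations and sample size: "under two-sided testing at alpha = 0.05"; RC 10% v 5.3% at effective N 1000 (Aim 1); 26% v 14.9% at effective N 424 (Aim 2). The two-proportion formula with equal arms gives power 0.799 and 0.811, so the claim to "ensure at least 80 % power to detect clinically significant effects for the main outcomes in the analyses for Aims 1 and 2" reproduces. For outcomes specified in SD units, power is Φ(δ√N/2 − 1.96):
- 0.20 SD at N 1000: Φ(3.162 − 1.96) = 0.885 (0.840 on a t reference with 15 df).
- 0.35 SD at N 424: 0.950 (0.920 with 15 df).

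These outcomes therefore exceed 80% power before any covariate is added.

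**2. Further inputs.**
- From the document: 3600 women, 17 clusters split 8 and 9, recent IPV at baseline 17%, within-clinic correlation no higher than 1%.
- Assumed, not in the document: equal clusters of m = 3600/17 = 212; correlation ρ = 0.01 for the baseline indicator as well as the outcome; a yes/no baseline abuse indicator with p = 0.17; women with baseline abuse score d = 0.5 to 1.0 SD higher on the outcome.

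**3. Chance imbalance in baseline prevalence (Aim 1).**
- Variance of a cluster mean = p(1−p)[(1−ρ)/m + ρ] = 0.1411 × (0.004675 + 0.01) = 0.00207.
- SE of the arm difference = √(0.00207 × (1/8 + 1/9)) = 0.0221, or 2.2 percentage points.

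**4. What passes the p < .20 screen.** The form of the test is not stated.
- Normal cut-off: 1.28 × 2.21 = 2.8 points. With 15 df: 1.34 × 2.21 = 3.0 points.
- Shift in the outcome contrast: 0.028 × 0.5 = 0.014 SD up to 0.030 × 1.0 = 0.030 SD, which is 7 to 15% of the 0.20 SD target.

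**5. Precision.**
- Person-level R² = p(1−p)d² = 0.035 to 0.141 (correlation about 0.19 to 0.38).
- Person-level share of cluster-mean variance = 0.004675/0.014675 = 32%.
- Fall in variance of the contrast = 0.32 × 0.035 to 0.32 × 0.141 = 1.1 to 4.5%. The SE falls by 0.6 to 2.3%.
- Power at 0.20 SD moves from 0.885 (N 1000) to 0.889 (1000/0.989 = 1011) up to 0.899 (1000/0.955 = 1047).

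This takes the covariate to explain no between-cluster variance. If it explained that part in the same proportion, the fall would be the full 3.5 to 14%.

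**6. Cross-check on a wider assumed range.** Take correlations r = 0.1 to 0.5 and let the whole effective sample size scale by 1/(1−r²), which is generous.
- Aim 1: the SE falls by 0.5 to 13.4% and power rises from 0.885 to between 0.888 and 0.955. Imbalance passing the screen is at most 1.28 × 2/√1000 = 0.081 SD of the covariate, a shift of 0.008 to 0.041 SD.
- Aim 2: 1.28 × 2/√424 = 0.124 SD of the covariate (severity), a shift of 0.012 to 0.062 SD, or 4 to 18% of 0.35 SD. The effective N of 424 is for pooled follow-ups and does not apply to disclosure, which is asked at T3 only.

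**The case against.** A reader might infer that chance imbalance in baseline abuse is simply left in these four contrasts. The documents do not support that. T1 RC and IPV are the baseline values of the primary outcomes, so they fall naturally among the key baseline measures compared between arms, and an imbalance of 1.96 SE would trip the p < .20 rule. Only the remainder in step 4 of the working escapes.

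Nor does the text exclude the T1 scores from other models. It names them for their own, and the Overview lists precision as a general purpose of covariates. What stands is that the only explicit routes for any other covariate are observed imbalance and confounding, and neither selects for precision.

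A reader might also turn R² into 4 to 16% more women, from 1/(1 − R²) − 1. That overstates the gain: with 17 fixed clusters, about two thirds of cluster-mean variance is between clusters on these assumptions.

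The prevalence figures do not carry over to resource use and disclosure, which are analysed only in women positive for IPV or RC at baseline. Only severity varies there. The link is also likely to be weaker for resource knowledge, which asks about information received, because the intervention gives resources to all clients.

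The full covariate list may be in an analysis plan that is not shown, and if it names these scores the point is met. But the article does state covariate rules and applies its proxy reasoning to one outcome only.

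Finally, the chart review records "documentation of any disclosures of IPV or RC" from 12 months before baseline, which looks like a ready proxy for disclosure. It is not a safe one. Staff were trained about 1 to 3 months before data collection, so in intervention clinics the look-back overlaps post-training care and may already reflect the intervention.

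**Conclusion.** The point holds as a modest improvement in prespecification, not as a flaw that threatens validity. Four outcomes lack both a baseline value and a named proxy, and the best available covariates reach their models only through a screen on observed imbalance. With an assumed 0.5 to 1.0 SD link and a within-clinic correlation of 0.01, naming the covariates cuts the variance of the Aim 1 contrasts by roughly 1 to 4.5%. It also removes imbalance worth at most about 0.014 to 0.030 SD. The documents give no correlation, so these figures are illustrative, and linear-model gains are only approximate for counts and binary outcomes. Power on the plan's own assumptions is adequate without the change. The case is strongest for harm reduction use, weaker for resource knowledge, and limited to baseline severity for resource use and disclosure.

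**What to change.** Add one sentence to the analysis plan: the T1 RC and IPV summary scores are covariates, regardless of the p < .20 screen, in the models for use of harm reduction strategies and knowledge of resources, and, as baseline severity, in the Aim 2 models for use of resources and disclosure. Keep general self-efficacy for the self-efficacy model. Do not add chart-documented pre-baseline disclosure.

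The cost is two patient-level parameters per model, which use no cluster-level degrees of freedom. There is also some reliance on imputed values for women whose T1 survey did not collect the RC and IPV items. The Missing data section already plans that imputation for baseline covariates, and the primary-outcome models already need it.

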#### Knowledge of IPV-related resources and services

To assess knowledge of IPV-related resources and services, participants are presented a list of resources and asked to endorse each one for which they “had received information on in the past 3 months” (Cronbach alpha = 0.80). Listed resources included Domestic Violence Advocacy Services, Rape Crisis Center, National Domestic Violence Hotline, Teen Dating Abuse Helpline, and Loveisrespect.org. A summary score is calculated with one point per resource selected for a maximum score of 5. To reduce the possibility of participants endorsing items because they had seen the resources identified in earlier surveys, this measure was not included in the baseline survey.

#### Additional secondary outcomes for women with recent history of IPV or RC

In addition to the above outcomes, two additional outcomes are included for analyses restricted to women who endorsed any physical or sexual violence or RC at baseline, as this group was hypothesized to receive the greatest benefit from the intervention. For convenience, we refer to this analysis subset as the “Aim 2” analysis, with the full population analyses described as “Aim 1” analyses.

#### Use of IPV-related resources and services

Participants are asked to endorse all IPV-related resources that they used in the past 3 months from the same list presented in the measure of knowledge of IPV-related resources and services (above) (Cronbach alpha = 0.55). As with the knowledge measure, this question is presented at follow-up visits only (T2 and T3). The outcome is modeled as a summary score, tallying number of endorsed items.

*Disclosure to a health care provider* was assessed at T3 only with two questions: whether in the past 12 months the client told a health care provider about ever being in an unhealthy or unsafe relationship or about a partner trying to get her pregnant when she didn’t want to be, messing with birth control, or controlling a pregnancy.

### Setting

Patients were recruited from 25 family planning clinics affiliated with Planned Parenthood of Western Pennsylvania and Adagio Health from both urban and rural areas within a 150 mile (3 h) radius of Pittsburgh, Pennsylvania. All were free-standing family planning clinics; family planning services embedded within community health centers were excluded. Some clinics were combined into clusters (*n* = 17 clusters) to account for shared staff and providers that could otherwise lead to contamination between the two arms of the trial.

### Randomization procedures, including choice of unit of randomization

The unit of randomization was clinic clusters comprised of one or a small number of clinics sharing a common set of healthcare providers. We chose a clinic-level cluster-randomized design to prevent contamination of the control condition (standard of care). Given that a main component of this intervention was training health care providers how to facilitate conversations with patients about threats to reproductive and sexual health (such as RC and IPV), it would not be feasible or appropriate to request a provider to initiate conversations with only a subset of patients, which would be the case if the study had used individual client-level randomization. A second component of the intervention was to connect clinics to domestic violence advocates to facilitate referrals to community violence resources; this clinic-level component precluded the use of provider-level randomization. The study was also intended to assess the effectiveness of this intervention in “real world” clinical settings, i.e., with expected variability in staff and provider comfort in addressing IPV and RC and implementation of the intervention.

To ensure balanced assignment by clinic setting, each cluster was labeled as urban or rural based on Census and Department of Commerce Federal Register data [60]. Clinics with common providers were clustered together. Randomization was stratified by cluster size and was designed to give each cluster an even probability of being randomized to intervention or control condition. Nine of the 10 single-clinic clusters were rural, with five randomized to treatment. Of the 6 two-clinic clusters, 2 were rural, 1 was urban and 3 were mixed. The randomization assigned the three mixed clinics to the control condition. The single 3-clinic cluster was all rural. It was assigned to the control condition, as well. Had the randomization resulted in a between-arm imbalance of 5 or greater rural clinics (a 16.25 % probability), it would have been discarded and a new randomization performed. Randomization was performed using SAS software by the study’s lead statistician ([name]).

### Participants: eligibility, recruitment and institutional review board requirements

#### Description of IRB approval

The study was approved by the University of Pittsburgh Institutional Review Board (IRB) on June 21, 2011 by expedited review (Protocol Number PRO11050458). The University’s IRB approval included a waiver for the requirement to obtain a written informed consent to participate in the research, in order to reduce the risk for breach of confidentiality (considered the primary risk associated with this study); women were offered a copy of an information sheet that was reviewed verbally with all clients. For minors ages 16 and 17, a waiver of parental informed consent for research participation was also approved by the IRB to protect youth seeking confidential services at these clinics from breach of confidentiality. A federal Certificate of Confidentiality was also obtained for the study to protect research records from subpoena.

Additional safety precautions were in place to reduce risk of harm to women for participating in the study, consistent with international recommendations and best practices on violence-related research [90]. Women who were at the clinic with a male partner were only approached about the study when they were alone. All follow up contacts made about the study referred to the study as the “Women’s Health Study.” To mitigate risk for emotional distress potentially associated with taking a survey about IPV, all research assistants were trained to ask women about how they were feeling after taking the survey, offer a list of community resources (with IPV and sexual assault information embedded among other less sensitive information about housing and food), and to suggest women speak with the clinical staff on site if they wished to talk more about the survey questions. Additionally, if any woman disclosed to a research assistant during survey administration that she was concerned about her safety, research assistants were trained to connect women with clinical staff as well as the local victim service advocacy organization. Finally, for follow up surveys conducted via email, women were encouraged to find a computer in a private space to complete the survey and to erase the history after survey completion. For those completing a follow up survey by phone, the research coordinator would suggest a special ‘code phrase’ the woman could use if she needed to hang up because someone else could overhear the conversation.

